### Analysis of process data

#### Intervention exposure

Participation frequency in the intervention groups serves as a measure of intervention dosage, and is expected to be related to the impact of the intervention. Participation will be examined both as a continuous and categorical measure, with intervention mothers being categorized into low, medium, high and non-participant groups. However, because there are likely to be confounding factors, such as demographics and maternal characteristics, that affect likelihood of participation, propensity scores corresponding to predicted attendance will be calculated for all mothers in the *Legacy* program. These scores will be used in dose–response analyses of primary outcomes to match intervention mothers with comparison mothers predisposed to the same level of participation (had they been randomized to intervention), balancing factors related to mothers’ ability to participate. In addition, qualitative process data related to retention and attrition will be examined.

#### Qualitative data

Ethnographic field notes made up a significant portion of *Legacy’s* qualitative data. A first purpose of the process data throughout the intervention was to provide feedback to the intervention sites on maternal responses to the intervention. For this analysis, the ethnographers reviewed their notes for major themes and observations, which were then compiled into monthly reports and shared with the intervention sites. Organized around *Legacy’s* major themes, the reports provided a narrative around the development of a sense of community among participants, parental self-efficacy, program response, and group dynamics.

For summative purposes, all ethnographic field notes were then themed and coded by trained coders from the PCC. During the pilot phase, the coding system was revised to accommodate new categories and themes, suggested by additional analysis of the data and field notes. Other forms of secondary analyses include case studies of individual participants, following the progress of selected participants over time, group case studies, following specific groups over time, and analyses of participant engagement.

### Analysis of cost data

Cost analyses will include both simple descriptive analyses and cost-effectiveness analyses to assess the cost per unit of outcome achieved. To date, cost estimates have been generated by site, type of intervention research activity (e.g., parent group meetings, visits to the home, and transportation), and at the family level. If participation in *Legacy* suggests improved outcomes among intervention participants, key outcomes will be identified to assess the intervention costs for unit increases in outcomes. Cost-effectiveness analysis is limited, however, in that multiple outcomes cannot be combined into a single measure of effectiveness. To overcome this limitation, estimates of cost savings may be summed from the literature for a number of outcome changes observed during and after the *Legacy* intervention. These estimated cost savings (benefits) could be compared to the costs of intervening to help assess whether the benefits of *Legacy* justify the costs.

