### Study hypotheses

The ultimate goal for *Legacy* was to improve outcomes for children along a broad spectrum of developmental domains. Therefore, the primary research question was: Do the children of mothers in the intervention groups achieve better developmental outcomes than do the children of mothers in their respective comparison groups?

A corollary set of questions asked in research of this type involves measuring corollary effects associated with the intervention. Thus, supplementing the main research question were five related questions.

Q1. Do mothers become engaged in the intervention program?

Q2. Do mothers adopt parenting behaviors more likely to foster child development?

Q3. Do the site adaptations of the model have similar or different effects on the measured outcome variables?

Q4. Do mothers in the intervention program develop a greater sense of community?

Q5. What are the costs of delivering the intervention and do the potential long-term benefits outweigh the costs?

Of these, Q2-5 involve comparing intervention and comparison groups, whereas Q1 will involve an analysis of intervention data only.

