## Methods/design

### Evaluation aims

Based on the initial review of early intervention research, internal and external expert input, and the development of the *Legacy* model, five related study aims were identified:

Aim 1: Document the implementation of the *Legacy* intervention and evaluate intervention fidelity.

Aim 2: Determine the relationship between self-efficacy and sense of the community and positive maternal-child interaction among the *Legacy* intervention mothers versus the comparison group mothers.

Aim 3: Evaluate the long-term goals of the intervention by examining the developmental outcomes of the children of the *Legacy* intervention mothers versus the comparison group mothers, in the domains of cognitive, language, socio-emotional, and behavioral development.

Aim 4: Understand how mothers responded to the intervention and which factors affected the quality of intervention each mother received.

Aim 5: Determine the costs associated with the group-based intervention in order to calculate overall costs and, if the intervention yielded significant effects, cost-benefit and cost-effectiveness indices.

These aims were executed, in concert with the Legacy Logic Model (Figure 2).

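### Two conflicting, results-dependent triggers for the economic indices: the benefit-versus-cost half of Q5 can lapse, and the effect in the cost ratio is selected on the results

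*Protocol article*

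**What the plan says.** Four places in the protocol article bear on this.

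- Study hypotheses, question Q5, has two parts: "What are the costs of delivering the intervention and do the potential long-term benefits outweigh the costs". The article adds: "Of these, Q2-5 involve comparing intervention and comparison groups".
- Evaluation aims, Aim 5, makes the first part unconditional: "Determine the costs associated with the group-based intervention in order to calculate overall costs". It then adds the indices under a condition: "if the intervention yielded significant effects, cost-benefit and cost-effectiveness indices".
- Analysis of cost data opens with no condition: "Cost analyses will include both simple descriptive analyses and cost-effectiveness analyses to assess the cost per unit of outcome achieved". Two sentences later the condition is "If participation in *Legacy* suggests improved outcomes among intervention participants", and in that case "key outcomes will be identified to assess the intervention costs for unit increases in outcomes".
- The same section says that, for a cost-benefit comparison, "estimates of cost savings may be summed from the literature for a number of outcome changes observed during and after" the intervention.

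The cost section names no effectiveness outcome. Under Sample size and power, the article does single out one measure, the age-appropriate cognitive score at age five.

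**The concern.** The triggers do not agree. One is statistical significance, one is apparent improvement with no threshold, and one sentence sets no condition at all. An analyst could follow any of them and be in line with the article.

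Both conditional versions also make the economic result depend on the effect estimate. Cost per unit is cost divided by effect. If the ratio is reported only when the estimated effect is large enough, the reported effects are a selected set whose average exceeds the truth. If the outcome itself is identified after the results are known, a second selection can be added. Where the true effect is modest, the cost per unit then looks lower than it is.

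If the condition is not met, the question whether benefits outweigh costs gets no estimate. Yet a small or null effect, with its uncertainty set against a known cost, would itself answer that question. The Discussion says that the results on effects, process and costs are meant to inform public policy.

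**Working it through.** **Inputs.** Design effect 0.50 SD, one-sided alpha 0.05, 120 evaluable children per site, stated power 0.86, and effects below 0.25 SD in earlier parenting programmes (Sample size and power). Year 5 sizes of 117/73 in Los Angeles and 122/73 in Miami (Table 4). Four child outcome domains (Aim 3). The article gives no cost-effectiveness figure to reproduce.

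**The plan's own power.** With 60 per group, SE = √(1/60 + 1/60) = 0.183 SD and 0.50/0.183 = 2.739. Power = Φ(2.739 − 1.645) = 0.863, which matches 0.86 (3:2 allocation, 72/48: 0.850; two-sided test: 0.782). The one-sided 0.05 test is therefore the planning test and is the natural gate to examine.

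**Gate at Los Angeles Year 5.** SE = √(1/117 + 1/73) = 0.149 SD. The smallest estimate that passes is c = 1.645 × 0.149 = 0.245 SD one-sided, or 1.96 × 0.149 = 0.292 SD two-sided.

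**Mean reported effect, one fixed outcome.** With true effect d and a = (c − d)/SE, the mean estimate given that it passes is d + SE·φ(a)/(1 − Φ(a)).

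- d = 0.25, one-sided: a = −0.031; 0.25 + 0.149 × 0.399/0.512 = 0.366 (46% too high).
- d = 0.25, two-sided: a = 0.284; 0.25 + 0.149 × 0.383/0.388 = 0.397 (59% too high).
- d = 0.50, one-sided: a = −1.71; 0.50 + 0.149 × 0.093/0.956 = 0.514 (3% too high). Two-sided: 0.525 (5% too high).

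**Mean cost per SD.** With cost fixed, reported cost per SD relative to the truth is d divided by the estimate. Its mean over the estimates that pass is:

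| True effect | Gate | Chance of passing | Mean reported effect | Mean cost per SD (truth = 1) |
|---|---|---|---|---|
| 0.25 | one-sided | 0.51 | 0.366 | 0.72 |
| 0.25 | two-sided | 0.39 | 0.397 | 0.65 |
| 0.50 | one-sided | 0.96 | 0.514 | 1.05 |
| 0.50 | two-sided | 0.92 | 0.525 | 1.01 |

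At 0.50 the ratio exceeds 1 because almost every estimate passes and the mean of a reciprocal exceeds the reciprocal of the mean. Miami (122/73) is nearly the same: 0.73 at a true 0.25 with the one-sided gate.

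**If the best of four outcomes were used.** This is a simulation at 117/73 with a one-sided gate, assuming four candidates, equal true effects and correlations of 0.3 to 0.7. At a true 0.25 the mean reported effect is 0.39-0.41 and cost per SD is 0.65-0.67 of the truth. At a true 0.50 cost per SD is 0.83-0.90 of the truth. At a true effect of zero, 12-16% of trials still yield a significant best outcome, and so a finite cost per unit for no gain.

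**The looser trigger.** The article sets no threshold for results that suggest improvement. As an illustration, suppose any estimate above zero counts. At a true 0.25 with one fixed outcome, a = −0.25/0.149 = −1.68, and the mean is 0.25 + 0.149 × 0.098/0.953 = 0.265, only 6% too high. Choosing the best of four without any gate gives 0.33-0.38. Under this trigger the later choice of outcome matters more than the gate.

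**The case against.** Several points on the other side are sound.

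- A reader might infer that Q5 as a whole goes unanswered without significance. It does not. Aim 5 calculates overall costs regardless, and the cost section reports that estimates by site, activity and family already exist. Only the benefit-versus-cost half can lapse.
- A reader might infer that significance is the one stated gate. It appears only in Aim 5. The cost section asks for suggested improvement and opens with an unconditional plan.
- A reader might infer that the cost ratio always flatters the programme. With one fixed outcome at the design effect of 0.50 SD, the gate makes mean cost per SD 1-5% too high at the Year 5 sizes, not too low.
- A reader might infer that the largest effects will be picked. The article says when outcomes are identified, not that the best ones are taken, so the best-of-four figures describe an assumed practice.
- A reader might infer that summed savings count the same gain twice. The wording there is tentative and prescribes no overlapping benefit streams. Overlap is a risk to guard against and not an error in the plan.

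It can also be said that a condensed article leaves the effectiveness unit and the uncertainty method to a fuller document, and that Q5 is a supplementary question. The missing uncertainty method is indeed no defect here. But the conditions on the results, and the timing of the choice of outcomes, are stated in the article. They are not omissions, and detail elsewhere would have to contradict them to remove the problem.

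**Conclusion.** The point stands in limited form. Aim 5 and the cost section disagree on when the indices are calculated. Either trigger can leave the benefit-versus-cost half of Q5 without an answer, and either makes the effect in the ratio depend on the results.

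The size of the bias depends on the true effect. At 0.25 SD, the upper end of what earlier parenting programmes showed according to the article, a significance gate on one fixed outcome understates mean cost per SD by about 28% one-sided or 35% two-sided. At the design effect of 0.50 SD it does almost nothing. Best-of-four selection would bring the understatement to 33-35% and 10-17% respectively, if that were the practice.

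These figures rest on normally distributed estimates, a fixed cost and the Los Angeles Year 5 sizes. The best-of-four figures also rest on equal true effects and the assumed correlations. The consequence is confined to a supplementary economic question. The randomised comparisons of child outcomes are not affected.

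**What to change.** Reconcile Aim 5 with the section on analysis of cost data, and remove both the significance condition and the improvement condition. Name the effectiveness outcome independently of the results; the age-five cognitive measure used for the sample size is an obvious candidate. For each site, report incremental cost and incremental effect with their joint uncertainty (for example a bootstrap interval or an acceptability curve), whatever the p-value. Presenting the two components together also copes with an effect near zero, where the ratio alone is unstable. As a caution, any sum of savings should list its benefit streams and count each once.

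The cost is a change of wording and a reanalysis of cost and outcome data already collected. The downside is that the economic results will be wider and may be unfavourable.

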## Discussion

### Strengths and unique contributions

The societal costs of poor developmental outcomes, including the personal costs to the individual and their families, are substantial and include medical, education, child welfare, social services, juvenile crime, and productivity loss. A concerted effort from multiple sectors and multiple disciplines, including public health, is necessary to address these societal concerns.

The CDC, in collaboration with other Federal and private partners, developed *Legacy* as a public health model to engage parents and promote evidence-based strategies that may contribute to overall child well-being in families in poverty. The results of the thorough evaluation of intervention effects, process, and costs will inform public policy on early intervention, health and well-being and help to address health disparities issues in at-risk populations.

### Study limitations

The *Legacy* study was designed as a rigorous trial of the intervention model, maximizing the internal validity so that potential alternate explanations for the results could be ruled out. In doing so, there was a corresponding cost to the external validity of the results. This trade-off may limit the generalizability of findings in three ways. First, the study was only conducted in two sites and with specific populations. Because of the low number of non-Hispanic White participants (15% at LA and 1% at Miami), the results may have limited generalizability for this population. Second, as mentioned previously, participant loss rate within the intervention group was 30%. Although mechanisms were in place to minimize subject loss, and the final sample had sufficient power to conduct the major analyses, fine-tuned examination of all factors will not be possible even with this sizeable sample. The results will thus reflect the population represented by mothers and children who were willing and able to continue participation in the assessments. Third, although there may be different patterns of effects within the individual intervention groups, there was a practical need to allow a certain degree of movement across intervention groups. Examples for this need include schedule conflicts, such as a return to work, as well as the need to merge groups over time due to group attrition. Therefore, although of interest, it is neither practical nor appropriate to perform analyses that treat the individual intervention groups as primary units of analysis. Finally, because the intervention was varied and adapted for each site, and specifically allowed for further adaptation of the content to mothers’ responses and comprehension level, fidelity to the model was difficult to measure precisely. Results may therefore be specific to the implementations and adaptations of UCLA and UM; therefore site differences cannot be fully explained quantitatively.

## Abbreviations

ANOVA: Analysis of Variance; BSC: Building Sense of Community; CLATT: Creative Learning Activities for Time Together; FUN Club: Family Unity Network Club; ITT: Intent-to-treat; MST: Main Session Topic; PCC: Project Coordinating Center; PCTT: Parent Child Together Time; RCT: Randomized Controlled Trial; UCLA: University of California at Los Angeles; UM: University of Miami.

## Disclaimer

The findings and conclusions in this report are those of the authors and do not necessarily represent the official position of the Centers for Disease Control and Prevention.
